## Abstract

Background: The efficacy of upper limb (UL) robot-assisted therapy (RAT) on functional improvement after stroke remains unclear. However, recently published randomized controlled trials have supported its potential benefits in enhancing the activities of daily living, arm and hand function, and muscle strength. Task-specific and high-intensity exercises are key points in facilitating motor re-learning in neurorehabilitation since RAT can provide an assisted-as-needed approach. This study aims to investigate the clinical effects of an exoskeleton robotic system for UL rehabilitation compared with conventional therapy (CT) in people with subacute stroke. As a secondary aim, we seek to identify patients’ characteristics, which can predict better recovery after UL-RAT and detects whether it could elicit greater brain stimulation. Methods: A total of 84 subacute stroke patients will be recruited from 7 Italian rehabilitation centers over 3 years. The patients will be randomly allocated to either CT (control group, CG) or CT plus UL-RT through an Armeo^®^Power (Hocoma AG, CH, Volketswil, Switzerland) exoskeleton (experimental group, EG). A sample stratification based on distance since onset, DSO (DSO ≤ 30; DSO > 30), and Fugl–Meyer Assessment (FM)-UL (FM-UL ≤ 22; 22 < FM-UL ≤ 44) will be considered for the randomization. The outcomes will be recorded at baseline (T0), after 25 + 3 sessions of intervention (T1), and at 6 months post-stroke (T2). The motor functioning assessed by the FM-UL (0–66) will be considered the primary outcome. The clinical assessments will be set based on the International Classification of Function, Disability and Health (ICF). A patient satisfaction questionnaire will be evaluated in the EG at T1. A subgroup of patients will be evaluated at T0 and T1 via electroencephalography. Their brain electrical activity will be recorded during rest conditions with their eyes closed and open (5 min each). Conclusion: The results of this trial will provide an in-depth understanding of the efficacy of early UL-RAT through a whole arm exoskeleton and how it may relate to the neural plasticity process. The trial was registered at ClinicalTrial.gov with the registration identifier NCT04697368.

## 1. Introduction

Upper limb impairments occur in up to 85% of stroke survivors and may persist even after 6 months from the acute event in 55% to 75% of patients [1]. Among the strategies and recent trends in stroke rehabilitation, robotic technologies are garnering more interest and their applications in clinical routine are growing. Upper limb robot-assisted therapy (UL-RAT) has been proven to improve recovery of arm and hand ranges of motion and muscle strength, thus improving the ability to perform activities of daily living (ADL) [2].

Current opinions about neurorehabilitation strategies to facilitate re-learning and motor recovery have highlighted the importance of task-specific exercises with a high level of intensity and repetition [3]. Indeed, more than 1000 repetitions of upper limb exercise are needed to elicit neuroplastic modifications to address effective post-brain injury recovery [4]. In this context, UL-RAT would be able to provide patients with an assist-as-needed approach.

Although several national guidelines advise clinicians on the importance of UL-RAT for arm stroke recovery, its efficacy has not been totally established, with an important recent trial that failed to demonstrate the superiority of robotic training over intensive conventional arm training [5]. In particular, UL-RAT should have a different efficacy on arm recovery following different subjects’ characteristics, for example, those linked to basal impairment, time from stroke, and subject participation [6]. Indeed, more severely impaired subjects should have more chances to perform intensive and effective training than those that only carry out conventional training [7,8]. On the contrary, less affected subjects have the possibility to perform, even without a robot, adequate arm training in terms of dose and task specificity. Following these considerations, there is the need for a well-powered randomized controlled study (RCT) that identifies subject characteristics for exoskeleton-based UL-RAT [9,10] in subjects affected by stroke in their subacute phase.

Over the last few decades, there has been growing literature demonstrating that the brain is capable of substantial structural and functional reorganization after stroke. Indeed, although some recovery is known to occur spontaneously within the first months, there is growing evidence that neurorehabilitation, with regard to innovative approaches, may modulate neuroplasticity mechanisms, providing greater functional benefits in a larger population of stroke survivors [11]. To investigate the neurophysiological basis of recovery after brain damage, EEG could be of help [12]. Moreover, monitoring brain activity immediately after a stroke or during neurosurgery may be fundamental to achieving better outcomes and prognosis [13,14].

Recent data suggest that the most promising EEG quantifiers for predicting UL motor outcome following stroke are event-related measures [15], although spectral power analysis in some relevant bands and fractal dimension analysis are also promising [16].

The first aim of this RCT is to investigate the clinical effects in terms of improvement in the motor control of an exoskeleton-based UL-RAT added onto standard rehabilitation compared with the same amount of conventional arm training alone.

The secondary objectives of the study are (a) to evaluate the efficacy of UL-RAT on arm ability recovery and on subjects’ quality of life; (b) to evaluate its efficacy in terms of objectives robot measures; (c) to identify the characteristics of patients who may benefit more from UL-RAT in terms of age, onset admission interval, and upper limb impairment; and (d) to evaluate of the effects of UL-RAT on motor recovery measured by neurophysiological signals: muscle and neural modification measured by surface electromyography and high-density electroencephalography (in a subgroup of patients).

## 2. Materials and Methods

### 2.1. Study Design

This trial has been designed as a multicenter, single-blind (evaluator) longitudinal parallel group with stratified block randomization, according to the updated guidelines for reporting parallel group randomized trials (CONSORT) [17].

This RCT has been approved by the Ethical Committee (unique protocol ID: RP 20/08; protocol code: PowerUPS-REHAB) and registered at clinicalregistration.gov (ID: NCT04697368; accessed on 1 March 2023).

### 2.2. Participants (Recruitment)

Inclusion criteria: age between 18 and 85 years old; first-ever ischemic stroke verified by brain imaging (CT or MRI); severe or moderate upper limb hemiparesis according to their Fugl–Meyer Assessment Upper Limb (FM-UL) score (FM-UL ≤ 22; between 22 and 44, respectively); stroke in the subacute phase (≤60 days from the distance since onset—DSO); Modified Ashworth Scale (MAS) of the shoulder, elbow, and wrist < 3; and sufficient cognitive and linguistic level to understand the instructions and to provide informed consent to participate in the study.

Exclusion criteria: stroke located in the brain stem or cerebellum; unstable general clinical conditions; severe visual impairment; recent upper limb botox injection or an injection planned for the duration of the study; orthopedic or neurological disease altering paretic upper limb function; interruption of treatments (both conventional and UL-RAT) for 1 week or 5 consecutive sessions; and participation in other innovative treatment protocols for the upper limb.

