### 2.3. Sample Population and Randomization

Eighty-four subjects will be recruited from seven Italian inpatient rehabilitation centers over three years and randomly assigned into one of the following groups: experimental group (EG) receiving UL-RAT or control group (CG) receiving conventional treatment (CT). A sample stratification based on DSO (DSO ≤ 30; DSO > 30) and motor impairment (FM-UL ≤ 22; 22 < FM-UL ≤ 44) will be considered for the randomization.

The patients will be randomly assigned to one of the two groups using a web-based application for block randomization (www.randomization.com; accessed on 6 November 2022). In particular, we will use the block randomization method (block size = 4) in order to ensure balance in the sample sizes across groups over time. Regarding the masking description, the outcome assessor will be blind to the study protocol. Please see the consort flow diagram in Figure 1.

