### 2.4. Outcome Assessment

The subjects of both groups will be assessed clinically (intention to treat) by a physical therapist not involved in other phases of the study at baseline (T0), at the end of the treatment (T1), and at 6 months after the acute event (T2). See Figure 1.

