
## 3. Procedure

### 3.1. Control Group

The control group (CG), in addition to multidisciplinary rehabilitation, will follow 40 min of conventional upper limb rehabilitation. Each participant will perform a total of 25 ± 3 conventional upper limb treatment sessions with a frequency of 5 times a week for 5 weeks. Each session will consist of passive, active-assisted, and active exercises tailored for shoulder, arm, and hand motor rehabilitation. For a detailed description of the exercises scheduled, please see Table 1, which shows the Tidier Template for Intervention Description and Replication [19].

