### 3.2. Experimental Group

The experimental group (EG), in addition to multidisciplinary rehabilitation, will perform one session per day of exoskeleton-assisted UL-RAT through the Armeo^®^Power (Hocoma AG, CH) robotic system. Each participant will perform a total of 25 ± 3 treatment sessions with a frequency of 5 times a week for 5 consecutive weeks.

During the first session, the device will be adjusted to the patient’s arm size and the angle of suspension. The working space and the exercises will be selected once the upper limb has been fitted with the system. The selection of personalized exercises will be based on the motor skills of each patient, and the difficulty can be gradually increased during training. In particular, a course of exercises has been defined, in which the difficulty varies (the suspension rate; the level of assistance; and the complexity of movement (1D, 2D, and 3D)). The physiotherapist will choose the modality based on the patient’s motor skills (standardized and personalized training); see Table 1.

UL–RAT will be set for 25% of the total weekly regular rehabilitation, in addition to the remaining 75% of tailored multidisciplinary rehabilitation programs, including occupational therapy, speech therapy, and cognitive-neuropsychological therapy. As compared with EG, CG will receive the same amount of neuro-motor rehabilitation each day following traditional rehabilitation approaches.

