### 3.5. Data Analysis

The sample size was determined based on the data published by Calabrò et al. in 2017 [20]: using a statistical power of 80% and an alpha of 5% with a β error of 20%, we need 70 total subjects (35 EG and 35 CG). However, considering the potential drop-out rate, 20% more, i.e., a total of 84 patients (42 EG and 42 CG), should be enrolled. In the absence of standard values of reference in the literature for the evaluation of the neurophysiological effects of robotic treatment for an upper limb compared with conventional treatment, an interim analysis will be performed when we enroll at least 10 patients of the expected sample. Following the results of the analysis of the acquired neurophysiological signals, we will evaluate whether to continue the enrolment or re-evaluate the number of subjects to be recruited.

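### An interruption of trial treatment is listed as an eligibility exclusion although it can only occur after randomisation; applied as an exclusion, it conflicts with the stated intention-to-treat assessment

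*Protocol article*

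**What the plan says.** Section 2.2 of the protocol article (Participants, Recruitment) opens its second list with "Exclusion criteria: stroke located in the brain stem or cerebellum; unstable general clinical conditions". Later in that list, among characteristics that can be checked before enrolment, stands "interruption of treatments (both conventional and UL-RAT) for 1 week or 5 consecutive sessions".

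Section 2.3 says that patients will be "randomly assigned into one of the following groups: experimental group (EG) receiving UL-RAT or control group (CG) receiving conventional treatment (CT". Section 3.2 gives the experimental schedule: "Each participant will perform a total of 25 ± 3 treatment sessions with a frequency of 5 times a week for 5 consecutive weeks". Section 3.1 gives the control group the same pattern: "a total of 25 ± 3 conventional upper limb treatment sessions with a frequency of 5 times a week for 5 weeks".

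Section 2.4 states the assessment principle: "The subjects of both groups will be assessed clinically (intention to treat) by a physical therapist not involved in other phases of the study". The time points are baseline (T0), end of treatment (T1) and 6 months after the stroke (T2). No section says what follows when a randomised patient meets the interruption item.

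**The concern.** An eligibility criterion decides who may be randomised. This item cannot do that, because it depends on a treatment that starts after allocation. If a centre applies it as it is headed, its only effect is to take out patients who have already been randomised, selected by how continuously they were treated.

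Intention to treat keeps every randomised patient in the allocated group whatever the adherence. For a patient who misses five sessions in a row, section 2.2 read literally says excluded and section 2.4 says assessed. Seven centres could settle this differently.

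The primary outcome, FM-UL, is at stake. The interventions differ greatly (exoskeleton against therapist-led exercise) and only the evaluator is blinded, so interruptions may differ between arms in frequency and cause. If those who interrupt also recover less well, leaving them out makes their arm look better than it is. The choice of analysis set can still be made late, but T1 and T2 data that were never collected cannot be recovered afterwards.

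**Working it through.** **Step 1. When can the event occur?** Three points, set side by side, place it after randomisation.
- The item names UL-RAT together with conventional treatment.
- UL-RAT is what patients assigned to the experimental group receive (sections 2.3 and 3.2).
- The threshold of 1 week or 5 sessions equals one week of the trial schedule, which is 5 sessions per week in both arms (sections 3.1 and 3.2).

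An interruption of conventional care alone could in principle come before allocation, but the item as worded covers both trial treatments.

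**Step 2. What does the item do to a patient who meets it?** Its heading implies exclusion. Section 2.4 implies continued assessment in the allocated group. The text supplies no rule that links the two, so the conflict is certain only if the item is applied as an exclusion.

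**Step 3. The plan's own figures.** Section 3.5 gives 70 patients (35 per arm) for 80% power at alpha 5%, raised by 20%: 70 × 1.20 = 84, or 42 per arm. The 70 cannot be reproduced, because the article gives neither an effect size nor an SD. Solving backwards with a two-sided t test, 35 per arm at 80% power corresponds to a difference of 0.68 SD. The normal approximation gives (1.96 + 0.84) × √(2/35) = 0.67 SD. Sidedness is not stated; two-sided is assumed.

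**Step 4. Illustration of bias, true effect zero.** Let shares pE and pC be removed from the experimental and control groups, and let those removed do worse than those retained by g SD in both arms. Setting the full-arm mean to 0 gives 0 = (1 − p)m + p(m − g), so the retained mean is m = p × g. The spurious difference is therefore

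bias = (pE − pC) × g.

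The type I error comes from the noncentral t distribution with nE = 42(1 − pE), nC = 42(1 − pC) and noncentrality bias / √(1/nE + 1/nC). Every pE, pC and g is an assumption, since the article gives no interruption rates.

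| pE | pC | g (SD) | Bias (SD) | Type I error |
|---|---|---|---|---|
| 10% | 5% | 0.5 | 0.05 × 0.5 = 0.025 | 5.1% |
| 15% | 5% | 1.0 | 0.10 × 1.0 = 0.10 | 7.1% |
| 20% | 5% | 1.0 | 0.15 × 1.0 = 0.15 | 9.7% |
| 10% | 10% | 0.5 or 1.0 | 0 | 5.0% |

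For the third row, nE = 33.6, nC = 39.9, the standard error is √(1/33.6 + 1/39.9) = 0.234 and the noncentrality is 0.15/0.234 = 0.64. The 0.10 SD bias of the second row is 0.10/0.68 = 15% of the back-solved design effect.

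The formula is symmetric: if more controls than experimental patients are removed, the bias changes sign.

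**The case against.** The strongest reply is that the item is an adherence or treatment-withdrawal rule placed under the wrong heading. On that reading a patient who interrupts stops trial treatment but is still seen at T1 and T2, and sections 2.2 and 2.4 coexist. The one explicit statement of principle is intention to treat, the article cites CONSORT, and analysis sets are commonly left to a statistical analysis plan, which is not shown here.

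Much of this stands. A reader might infer that the protocol certainly drops such patients from the primary analysis, or that the two sections can never both be followed. The text supports neither, because it is silent on what happens after an interruption. Nor is the absence of a per-protocol definition a fault in an article.

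A reader might also infer that the bias must favour the robot. The document does not show that. Both arms are inpatients on the same session schedule, so medical causes of a one-week gap may be largely shared. The wording could also mean that both treatments stop together, in which case robot downtime alone would not trigger it. The larger error rates need a three- or fourfold excess of interruptions in the experimental group plus a full 1 SD gap in outcome, and nothing in the document supports either.

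What does not stand is the idea that nothing needs changing. Even on the benign reading the item is in a list where it cannot operate, and a centre that follows the list literally would act against section 2.4.

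**Conclusion.** The point holds in a conditional form. The item is wrongly placed: it is a post-randomisation event listed as an eligibility exclusion. Applied as one, it selects randomised patients by adherence and contradicts the intention-to-treat assessment. Whether that would happen cannot be told from the article.

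The misplacement rests on the wording alone and depends on no number. The consequence has no known size or direction. The illustrated range, a type I error from about 5.1% (practically nominal) to 9.7%, rests wholly on the assumed removal shares and outcome gap, a common gap in both arms and a two-sided 5% test. It shows what could happen and is not an estimate for this trial. The correction is still worth making before follow-up is lost, because it decides who contributes to the primary FM-UL comparison.

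**What to change.** Reconcile sections 2.2 and 2.4:

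1. Take the interruption item out of the eligibility exclusions and describe it as a post-randomisation adherence event, recorded with its date and reason.
2. State that an interruption neither ends the T1 and T2 assessments nor removes a patient from the primary FM-UL analysis, which is made in the allocated group.
3. Use the threshold of 1 week or 5 sessions only to define a secondary analysis, labelled per-protocol.

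Simply deleting the item would go too far, since it may also serve as a treatment-stopping rule. Whether trial treatment continues after an interruption is a matter for the investigators and is not touched here.

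The cost is a short amendment, T1 and T2 assessment of a few more patients, and slight dilution of the estimated effect, because incompletely treated patients stay in the comparison. The planned 84 patients (42 per arm) do not change.

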### 2.3. Sample Population and Randomization

Eighty-four subjects will be recruited from seven Italian inpatient rehabilitation centers over three years and randomly assigned into one of the following groups: experimental group (EG) receiving UL-RAT or control group (CG) receiving conventional treatment (CT). A sample stratification based on DSO (DSO ≤ 30; DSO > 30) and motor impairment (FM-UL ≤ 22; 22 < FM-UL ≤ 44) will be considered for the randomization.

The patients will be randomly assigned to one of the two groups using a web-based application for block randomization (www.randomization.com; accessed on 6 November 2022). In particular, we will use the block randomization method (block size = 4) in order to ensure balance in the sample sizes across groups over time. Regarding the masking description, the outcome assessor will be blind to the study protocol. Please see the consort flow diagram in Figure 1.

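### One fixed, published block size of 4 in a trial blinded only at assessment is an avoidable risk to allocation concealment; how large a risk depends on a list structure the article does not state

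*Protocol article*

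**What the plan says.** - **Design** (section 2.1): "multicenter, single-blind (evaluator) longitudinal parallel group with stratified block randomization".
- **Blocks** (section 2.3): "we will use the block randomization method (block size = 4"), with the stated aim of keeping the group sizes balanced as recruitment proceeds. No second size and no random variation of size is mentioned.
- **Tool** (section 2.3): allocation is made "using a web-based application for block randomization (www.randomization.com; accessed on 6 November 2022").
- **Strata** (section 2.3): "A sample stratification based on DSO (DSO ≤ 30; DSO > 30) and motor impairment (FM-UL ≤ 22; 22 < FM-UL ≤ 44"). That is 2 × 2 = 4 strata. Centre is not named as a factor.
- **Size and sites** (sections 2.3 and 3.5): "Eighty-four subjects will be recruited from seven Italian inpatient rehabilitation centers over three years"; "a total of 84 patients (42 EG and 42 CG), should be enrolled". Allocation is therefore 1:1.
- **Masking** (sections 2.1 and 2.3): the assessor only. Section 3.2 and Table 1 describe fitting the exoskeleton to the patient, so treating staff know the arm.

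The article does not say whether lists are kept per centre or shared, who holds them, or whether those who enrol patients are also those who see earlier allocations.

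**The concern.** With 1:1 blocks of one known size, the past allocations in a block constrain the next one. The fourth is always determined, and the third is determined whenever the first two agree. In an open-label trial, someone who recruits and can also follow the list could therefore sometimes know the next arm before deciding whether, or when, to enrol a patient.

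Section 2.2 leaves room for such steering. Adequate cognition and language, and clinical stability, are matters of judgement, and the 60-day window makes the timing of enrolment flexible. The Discussion names spontaneous recovery as the main driver of recovery trajectories, so selecting patients by expected recovery would act directly on FM-UL, the primary outcome. Stratifying by two bands of time since onset and two bands of FM-UL leaves prognosis within each stratum open. The blinded assessor protects the measurement; it does not protect the choice of who enters which arm.

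**Working it through.** The article gives no figure for predictability, so there is none to reproduce. Inputs: block size 4, four strata and seven centres (section 2.3); 84 patients at 1:1 (section 3.5).

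**Step 1. One fully observed block of 4.** With *a* and *b* places left for the two arms, the best guess is right with probability max(a, b)/(a + b). An allocation is certain when a or b is 0.

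| Position | P(certain) | P(best guess right) |
|---|---|---|
| 1 | 0 | 2/4 = 0.500 |
| 2 | 0 | 2/3 = 0.667 |
| 3 | 1/3 | 1/3 × 1 + 2/3 × 0.5 = 0.667 |
| 4 | 1 | 1.000 |
| Mean | 1.333/4 = 33.3% | 2.833/4 = 70.8% |

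Over 84 patients in complete blocks, 84 × 1/3 = 28 allocations would be certain to an observer of the whole sequence.

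**Step 2. Effect of list structure (assumed, since it is not stated).**

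- *Four stratum lists, fully visible.* 84/4 = 21 patients per list, which is five full blocks plus one first position. Certain: 5 × 1.333/21 = 31.7%. Best guess: (5 × 2.833 + 0.5)/21 = 69.8%.
- *Separate lists per centre and stratum.* 7 × 4 = 28 lists, 84/28 = 3 patients each. Certain: (1/3)/3 = 11.1%. Best guess: (0.500 + 0.667 + 0.667)/3 = 61.1%. If list lengths vary at random around 3, the figures are about 19% and 64%, because longer lists contain completed blocks.
- *Four stratum lists shared by seven centres, each site seeing only its own patients.* Simulation with 21 patients per list and equal recruitment: about 52% right when guessing the arm that is behind at the site. If the site also knows each patient's position on the list, about 53% are right and under 1% are certain.

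**Step 3. Effect of varying the block size.** Simulated lists of 21, with an observer who sees the whole list and knows the set of possible sizes:

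| Block sizes | Certain | Best guess right | Largest end-of-list imbalance |
|---|---|---|---|
| 4 (as planned) | 31.7% | 69.8% | 2 |
| 4, 6 | 5.8% | 68.0% | 3 |
| 4, 6, 8 | 2.4% | 66.8% | 4 |
| 2, 4, 6 | 3.7% | 69.1% | 3 |
| 2, 4 | 10.4% | 71.1% | 2 |

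The largest imbalance is half the largest block. On lists of 3, the sets 4/6, 4/6/8 and 2/4/6 all bring the certain share from 11% to 0%. The best-guess rate there goes from about 61% to about 59% with 4/6 and about 58% with 4/6/8, while 2/4/6 leaves it at about 61%. Sets that include 2 gain little or nothing on the guess rate.

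**The case against.** The strongest reply is that the link between seeing a treatment and steering recruitment is not in the document. A therapist who fits an exoskeleton is not necessarily the person who enrols the next patient, and the article does not say that recruiters see earlier allocations. Custody of the list and the concealment procedure are details that an article commonly leaves to the full protocol. Since only two stratification factors are named, the literal reading is four lists shared by seven centres, and on that reading a single site gains almost nothing. A small fixed block also has a stated purpose, balance over time. FM-UL must be known before a patient can be assigned to a stratum, and section 2.4 gives the T0 assessment to a therapist with no other part in the study. Finally, varying the block size barely moves the best-guess rate, because guessing the arm that is behind needs no knowledge of block size.

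Most of this stands, and it limits the size of the point. A reader might infer that centre-level lists would push guessing towards 71%. They would not, because such lists average 3 patients, shorter than one block. A reader might also infer that concealment is absent. The document does not support that, and its silence on procedure is not a finding.

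What remains is the choice the article does state: one block size, published, in a trial where the arm is visible to staff. Whoever can follow a list gains certain knowledge from that choice, and varying the size removes most of it.

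**Conclusion.** The point holds as an avoidable weakness of modest and uncertain size. The share of allocations known in advance is about 32–33% for someone who sees a whole stratum list, about 11% with lists per centre and stratum, and close to none with shared lists of which each site sees only its own part.

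These figures assume 1:1 blocks of 4, equal strata of 21 patients, equal recruitment across centres, and an observer who uses the information. A reader might conclude that the trial is subject to selection bias, or that about 28 of the 84 allocations are known to recruiters. The documents support neither. The figure of 28 requires one observer of the complete sequence, and nothing in the article places a recruiter in that position. The case for changing the plan rests on the low cost of the change and on the open-label setting, not on any shown bias.

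**What to change.** Generate the part of the lists not yet used with randomly varying block sizes within the existing four strata: 4 and 6, or 4, 6 and 8, but not sets that include 2. Keep the sizes in a document that sites do not receive. Release each allocation only once eligibility and the T0 FM-UL are recorded; if the full protocol already requires this, a cross-reference is enough. The same passage could state whether lists are shared or per centre, which would settle how much the point matters.

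The varying sizes reduce predictability without removing it: best-guess accuracy for an observer of a whole list stays at 67–68%. That is why the release step matters as well.

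The cost is one amended sentence in section 2.3 and regenerated lists. Sample size, strata, endpoints and treatments do not change. The largest possible imbalance at the end of a list rises from 2 to 3 (sizes 4 and 6) or 4 (sizes 4, 6 and 8).
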